### Statistics

#### General descriptive statistics and preliminary data screening

Baseline demographics, clinical characteristics, and procedure-related information will be presented as median (25–75% interquartile range (IQR)) for continuous data elements and frequencies (%) for categorical data.

Accelerometer data will be preprocessed by the ActiLife [26] software to convert the raw accelerometer signal into expressions of movement and energy expenditure. These calculations require some basic patient information (e.g., weight), so the device configuration will be verified prior to finalization of the calculations. For the primary analysis, we will aggregate the summaries on a daily basis. For exploratory analysis we will use the summaries on a finer time resolution (e.g., minute to minute) to determine whether this provides a more sensitive method of detecting subtle changes in activity levels.

### Primary analysis

The primary outcome analyses will be performed using an “as treated” rather than an “intention-to-treat” analysis set while accounting for the crossover design. This approach is most appropriate for this pilot clinical trial, which primarily aims to understand home functional status as it relates to ambulatory RBC transfusion. For statistical comparisons, we will fit a random effects model that utilizes daily total energy expenditure as the dependent variable and days from transfusion or control visit (“placebo” visit where no transfusion was performed). For simplicity, we will include the mean daily measurements for the 3 days prior to the transfusion/control visit as covariates in the model, and consider the 7 days after transfusion/control visit in the model. This censoring of data beyond 7 days after the transfusion/control visit is to avoid carryover effects with the model. We will test the transfusion indicator by study day interaction, with adjustment for baseline activity, for the primary hypothesis. This parameter will quantify how the profile of activity differs with and without transfusion while accounting for the variation in activity between participants by means of the random effect and baseline adjustment. Contrasts will be constructed to quantify the difference in the change in activity between these visits.

Sensitivity analyses will attempt to model the change in activity levels in the days after transfusion. These exploratory models will consider a potential initial boost in activity with linear or exponential trends to account for the change in activity over the 7 days after transfusion. These models will also include subject random effect and account for time-series correlation. These analyses will be expanded to include all data measured over the 28-day period.

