### Blinding

Due to the nature of the intervention (transfusion versus no transfusion), blinding to the intervention will not be feasible for either the patient or the clinical team in this pilot clinical trial. The accelerometer does not provide any visual indication of activity levels (e.g., no step count or estimated energy expenditures), so participants will be blinded to the data accumulated by the device. With the exception of the Data Monitoring Committee, investigators will not have access to the accelerometer data until the completion of the trial. Patients may access their data after completion of the trial by request to the study team. Because blinding to the intervention is impossible, and because the purpose of the trial is carefully explained to participants beforehand, we note the potential for both performance and detection biases. In particular, many participants may have an expectation of lower functional status after a no-transfusion encounter. One downstream consequence of this is a potential bias towards lack of effect, meaning that transfusions may be biased to appear more effective than the no-transfusion intervention. Concerns related to selection bias are expected to be largely mitigated by randomization and by the crossover nature of the design. Nonetheless, risks related to residual biases resulting from unique characteristics associated with patients who consent to participate in this trial clearly remain.

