### Practice logistics and workflow

A critical component for the successful completion of this study is close integration with the current hematology and oncology practices at the AIC. From a practical perspective, engineering this integration has been the most challenging aspect of moving the study forward. Because of this, we detail our practice logistics and workflow model.

It is important to remember that in this protocol *not* transfusing the patient is the intervention – otherwise standard practice is followed. Thus, from a practice logistics and patient safety point of view it is during the no-transfusion arm that special care must be taken.

The current practice at the AIC is for patients receiving transfusion therapies (e.g., chemotherapy) to be associated with a set of standing orders by their practicing physician. These standing orders are typically directions to transfuse the patient when their Hgb is measured below a specific level. For many practicing physicians this Hgb level will be between 7.0 and 9.0 g/dL. These standing orders are specified for a defined time period up to 3 months so their modification is an important aspect of implementing the proposed protocol.

When a SC identifies a patient who appears to be a likely candidate, they will contact the potential study participant’s primary physician to receive conditional approval for inclusion in the study. Patients receiving conditional provider approval will have Hgb levels monitored on the day of their AIC visit by the SC. If the Hgb is within the range prescribed for transfusion, the patient is approached for screening and informed consent. If enrolled, the SC will randomize the participant. If the participant’s next encounter is to transfuse, no change to the standing orders is required.

If the patient’s next encounter is no-transfusion, new standing orders are requested. These orders are designed to avoid RBC transfusion unless specific “over-riding” RBC transfusion criteria are present. These “over-riding” RBC transfusion criteria include: acute ischemia (e.g., MI, CVA), Hgb <7.0 g/dL, active bleeding, and symptomatic anemia (hypotension, tachycardia, angina or syncope/presyncope believed related to anemia). If none of the above mentioned “over-riding” RBC transfusion criteria are present, the patient will not be transfused.

After the participant crosses from one study arm to the other, the SC requests new standing orders as necessary.

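### The primary analysis is as treated with no as-randomized analysis planned, although a no-transfusion assignment is overridden only when the patient is acutely worse

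*Protocol article*

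**What the plan says.** The Primary analysis section of the protocol article fixes the analysis set: "The primary outcome analyses will be performed using an “as treated” rather than an “intention-to-treat” analysis set while accounting for the crossover design". Its reason is: "This approach is most appropriate for this pilot clinical trial, which primarily aims to understand home functional status as it relates to ambulatory RBC transfusion". A control visit is defined by what was given, as a "visit where no transfusion was performed". The model has a participant random effect, takes the mean of the 3 days before each visit as a covariate and uses the 7 days after it. The test is specified as: "We will test the transfusion indicator by study day interaction, with adjustment for baseline activity, for the primary hypothesis". The sensitivity analyses in that section concern the shape of the activity profile and the full 28 days. None analyses visits by assigned condition.

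Practice logistics and workflow lists what overrides a no-transfusion assignment: "acute ischemia (e.g., MI, CVA), Hgb <7.0 g/dL, active bleeding, and symptomatic anemia (hypotension, tachycardia, angina or syncope/presyncope believed related to anemia"). Only visits with none of these stay untransfused. Table 1 excludes patients with the same conditions at enrolment.

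The Blinding section says: "Concerns related to selection bias are expected to be largely mitigated by randomization and by the crossover nature of the design". The secondary aims use the efficacy signal in deciding on a larger trial: strong evidence for transfusion makes one less likely, and an equivocal or opposite result makes one more likely.

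**The concern.** The reason for departing from a no-transfusion assignment is the patient's condition at that visit. Under the as-treated rule every such visit changes sides. What remains under control has been filtered for the absence of acute illness, while visits assigned to transfusion have not been filtered in that way. The two sets of visits then differ by selection as well as by transfusion.

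The crossover is affected too. If the overridden visit is kept, that participant has two transfusion visits and no control visit, and enters the random effects model only through between-participant information. Because Table 1 screens out the same conditions at enrolment, most overrides should fall at the second visit of the transfusion-first sequence, which ties the relabelling to period and sequence.

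At stake is the pilot's main estimate and the decision that it feeds. The stated rationale, an interest in function as it relates to transfusion, does not deal with why patients depart from assignment.

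**Working it through.** **1. The plan's own figure.** 12 per group x 2 = 24 evaluable; 24 x 1.25 = 30. The planned total reproduces, and the point does not depend on it.

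**2. Participants who could lose their control visit.** The override rate f is not in the article; 5% to 30% is assumed. If every no-transfusion visit is at risk, the expected number is 30f, or 1.5 to 9. If only the transfusion-first half is at risk, it is 15f, or 0.75 to 4.5.

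**3. Bias in the mean difference.** All parameters here are assumptions. Activity after a visit is u + 0.5h + e, where u is the participant effect (SD 0.7), h is health at the visit (SD 1, low is sick) and e is noise (SD 0.5). The 3-day baseline is u + 0.5h plus separate noise (SD 0.5). The true transfusion effect is 0. A no-transfusion visit is transfused when h lies below its f-quantile. The fitted model has a random intercept, period, transfusion, and optionally the baseline. The variance of activity is 0.49 + 0.25 + 0.25 = 0.99, so one simulation unit is about one SD of visit-level activity.

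As-treated estimates (the true value is 0):

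| Overrides possible at | Baseline covariate | 5% | 10% | 20% | 30% |
|---|---|---|---|---|---|
| Second visit only | yes | -0.016 | -0.024 | -0.036 | -0.047 |
| Second visit only | no | -0.035 | -0.062 | -0.098 | -0.129 |
| Either no-transfusion visit | yes | -0.027 | -0.042 | -0.075 | -0.099 |
| Either no-transfusion visit | no | -0.072 | -0.127 | -0.218 | -0.304 |

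The as-randomized estimate lay between -0.002 and +0.003 throughout.

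Hand check at 10%, either visit, no covariate: retained control visits have mean h = 0.1755 / 0.90 = 0.195 (the normal density at the 10% point divided by the share retained). A purely within-person comparison is therefore biased by -0.5 x 0.195 = -0.10. Overridden participants add between-person information, which moves the mixed-model estimate further, to -0.127.

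**4. The parameter actually tested.** The primary test is the transfusion-by-day interaction, so a mean difference is not the whole story. With seven daily values per visit and no true effect, illness that lowers all 7 days equally gives an interaction bias of 0.00 at 10, 15 and 25% override. If illness fades over the week, the relabelled sick visits rise from day 1 to day 7 and the transfusion profile rises with them: about +0.14 units in favour of transfusion at 15% override under one assumed fading pattern.

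**5. Rejection under the null at 24 participants.** It was about 0.07-0.08 as randomized and 0.07-0.09 as treated. The excess over 0.05 in both comes from the approximate small-sample test used. At this size the harm is a biased estimate more than a false positive.

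**The case against.** The as-treated choice is deliberate, disclosed and explained. The trial is a pilot sized to estimate a standard deviation, with no minimum relevant difference set. Selection bias is said only to be largely mitigated, and visits without an override keep their randomized label. The participant effect and the 3-day baseline absorb part of the difference in health. All of this stands, and it limits the size of the problem. It does not supply an as-randomized estimate or remove the selection.

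A reader might infer three stronger things that the article does not support:

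- **That the bias certainly runs against transfusion.** This needs illness to lower activity over the following week and refers to the mean level. For the tested interaction it may be zero or reversed.
- **That the bias is about -0.13 to -0.17 SD at 15% override, with about 4 of 24 participants losing their contrast.** This leaves out the baseline covariate and lets every no-transfusion visit be overridden (24 x 0.15 = 3.6). With the enrolment exclusions, about 12 x 0.15 = 1.8 participants is the better figure, and the bias is correspondingly smaller.
- **That healthier transfusion visits also move to control because hemoglobin has recovered.** No section describes this. Crossover takes place at a scheduled transfusion, and standing orders transfuse below a hemoglobin level, so such a visit need not be a study visit.

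It is also fair that the article does not say whether an overridden visit is kept, deferred, or treated as partial completion, for which Data monitoring removes the patient. Removal would be selective too, but it would be a different problem. Finally, the decision argument cuts both ways: an as-randomized estimate is diluted towards the equivocal result that makes a larger trial more likely.

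**Conclusion.** The point holds for the choice of analysis set. Followed as written, the plan compares visits partly sorted by acute illness and offers no randomized comparison beside it. It is a badly fixed choice, openly stated, and not a contradiction about which analysis is to be done.

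The likely size is modest: about -0.02 to -0.05 units in the mean difference with second-visit overrides and the baseline covariate, and up to about -0.10 if either no-transfusion visit can be overridden. This rests on an assumed override rate of 5-30%, an assumed link between health and activity, and a baseline that already reflects the illness. If the event starts on the visit day, the 3 prior days would not show it, and the figures without the covariate (-0.04 to -0.13 for second-visit overrides) are a closer guide. Confidence is high in the mechanism and limited in direction and size.

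**What to change.** Make the as-randomized analysis primary, with each visit analysed under its assigned condition whatever was given. Keep the as-treated analysis as a labelled sensitivity analysis. Report the number of overridden visits and their reasons by period and sequence, which is useful feasibility information in its own right. State whether an overridden visit stays in the analysis.

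The cost is wording. The assigned sequence is held in the REDCap randomization module, and transfusions given are captured through the weekly calls and the health record. The downside is that overridden visits dilute the as-randomized estimate; the as-treated result remains beside it. The clinical override criteria are not affected.

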**Methods/design:**

This will be a randomized crossover pilot clinical trial with a participant study duration of 28 days. The crossover nature allows each patient to serve as their own control. Briefly, patients presenting at a tertiary medical center’s Ambulatory Infusion Center (AIC) will be randomized to either: (1) receive an RBC transfusion as scheduled (transfusion) or (2) abstain from the scheduled transfusion (no transfusion). After an appropriate washout period, participants will crossover from the transfusion arm to the no-transfusion arm or vice versa. Activity levels will be recorded continuously throughout the study using an accelerometry monitor. In addition to device data, functional status and health outcomes will be collected via a weekly telephone interview. The primary outcome measure will be daily energy expenditure. Performance metrics, such as step count changes, will also be evaluated. Additional secondary outcome measures will include daily sedentary time and Patient-reported Outcomes Measurement Information System (PROMIS) Global 10 Survey scores.

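### The primary model's visit-level baseline, read as one covariate with one slope, costs precision in the between-visit contrast of 7-day activity; split it and add a visit-level error

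*Protocol article*

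**What the plan says.** The Primary analysis section of the protocol article specifies the model in some detail: "we will fit a random effects model that utilizes daily total energy expenditure as the dependent variable". For each visit, "we will include the mean daily measurements for the 3 days prior to the transfusion/control visit as covariates in the model", and the plan is to "consider the 7 days after transfusion/control visit in the model". The named test is this: "We will test the transfusion indicator by study day interaction, with adjustment for baseline activity, for the primary hypothesis". The section gives the purpose of the covariate as "accounting for the variation in activity between participants by means of the random effect and baseline adjustment". It then adds a between-visit estimate: "Contrasts will be constructed to quantify the difference in the change in activity between these visits".

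Three other places bear on the point.
- Specific aim 1 (Aims and objectives) states the hypothesis for the change in mean daily activity over 7 days, so it concerns a level and not a day-by-day profile.
- The abstract gives the reason for the design: "The crossover nature allows each patient to serve as their own control".
- Secondary endpoint analysis applies the same modelling to the other accelerometer endpoints.

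The primary model names no visit-within-participant effect. Serial correlation is mentioned only for the sensitivity models.

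**The concern.** In a crossover, pairing already removes stable differences between participants from the transfusion-minus-control difference. A baseline measured afresh at each visit carries two kinds of information.

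- **Between people**, it reflects stable activity level and body weight, so it predicts the 7-day mean with a slope near 1.
- **Within a person**, the difference between two 3-day means may be largely day-to-day noise, so its slope on the 7-day difference can be small.

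One slope has to serve both and settles on a compromise that can lie close to the between-person value. The within-person contrast is then over-corrected by a multiple of a noisy quantity.

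What is at stake is the contrast that answers Aim 1. An equal rise in activity on all 7 days produces no transfusion-by-day interaction, so only the between-visit contrast would show it. The Secondary objectives text uses the signal of efficacy, with feasibility and adverse events, to decide whether a larger trial is pursued.

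**Working it through.** **The plan's own figure.** Two groups of 12 give 24 evaluable participants, and 24 × 1.25 = 30, as stated. The protocol states no alpha, power, effect size or SD, so there is no power figure to reproduce.

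**Inputs.** From the protocol: 24 evaluable participants, 2 visits, 3 pre-visit and 7 post-visit days, simple 1:1 randomization to sequence. Assumed: two-sided alpha 0.05; independent days with SD 0.7; between-person SD 0.5, 1 or 2; visit-to-visit SD 0, 0.3 or 0.6; effect as stated below.

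**Step 1: the two slopes** (between-person SD 1, daily variance 0.49).
- Between people, using the mean of both baselines (6 days), no visit variance: 1/(1 + 0.49/6) = 0.92.
- Within a person, visit variance ω² fully shared by baseline and outcome: ω²/(ω² + 0.49/3). This is 0 at ω = 0; 0.09/0.253 = 0.36 at ω = 0.3; 0.36/0.523 = 0.69 at ω = 0.6.

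In simulation with ω = 0, the single-slope model fitted 0.64–0.65 with a participant effect only and 0.83 with a visit-level error, where the within-person slope is 0. At between-person SD 2 it fitted about 0.89 and 0.95–0.96.

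**Step 2: cost in precision, by hand** (ω = 0, visit-level error in the model).
- Variance of a participant's 7-day difference: 2 × 0.49/7 = 0.140.
- Variance of the baseline difference: 2 × 0.49/3 = 0.327.
- Subtracting 0.83 times the baseline difference: 0.140 + 0.83² × 0.327 = 0.365.
- SE of the contrast: √(0.365/24) = 0.123, against √(0.140/24) = 0.076 without it, a ratio of 1.61.
- For an effect of 0.22 these are 1.78 and 2.88 standard errors. Noncentral t power on 22 df is about 40% and 79%.

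**Step 3: false positives, by hand** (ω = 0, participant effect only). With slope 0.65 the true variance is 0.140 + 0.65² × 0.327 = 0.278, but the model's SE reflects roughly 0.140. The SE is too small by √(0.278/0.140) = 1.41, and 2 × Φ(−1.96/1.41) = 0.16.

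**Step 4: simulation** (REML, 1,000 trials per setting, 7-day mean contrast, daily SD 0.7, visit effect fully shared by baseline and outcome).

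Power with a visit-level error in the model:

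| Between SD | Visit SD | Effect | Single slope | Split | No baseline |
|---|---|---|---|---|---|
| 0.5 | 0 | 0.22 | 0.59 | 0.73 | 0.74 |
| 1 | 0 | 0.22 | 0.39 | 0.71 | 0.75 |
| 2 | 0 | 0.22 | 0.32 | 0.73 | 0.75 |
| 1 | 0.3 | 0.30 | 0.62 | 0.76 | 0.68 |
| 2 | 0.3 | 0.30 | 0.58 | 0.77 | 0.69 |
| 1 | 0.6 | 0.50 | 0.953 | 0.957 | 0.67 |

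Type I error for these models was 0.03–0.06 throughout.

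Type I error with a participant random effect only:

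| Between SD | Visit SD | Single slope | Split | No baseline |
|---|---|---|---|---|
| 0.5 | 0 | 0.088 | 0.044 | 0.037 |
| 1 | 0 | 0.158 | 0.060 | 0.062 |
| 2 | 0 | 0.207 | 0.062 | 0.058 |
| 1 | 0.3 | 0.185 | 0.143 | 0.164 |
| 2 | 0.3 | 0.214 | 0.145 | 0.174 |
| 1 | 0.6 | 0.216 | 0.192 | 0.363 |

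A separate run at between-person SD 1 gave type I error 0.11 (single) against 0.03 (split) and power 0.39 against 0.75 with no visit variance. With visit SD 0.3 and a pre/post correlation of 0.5, power was 0.60 against 0.81.

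**Step 5: the named test.** The baseline does not vary within a visit, so it drops out of comparisons between days. The 6-df interaction test rejected under the null in 0.020–0.059 of trials with one slope and 0.032–0.064 with the split. A joint test of seven day-specific transfusion effects, a looser reading of the same sentence, gave 0.06–0.09 with one slope and 0.05–0.09 with the split.

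**The case against.** Four objections carry weight.

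1. **The named primary test is untouched.** A reader might infer that the primary hypothesis test gives false positives. The documents do not support that: the interaction test is essentially unaffected (Step 5), and the between-visit contrast is introduced to quantify a difference, not as the formal test. This stands, and it limits the point to that contrast.

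2. **The single slope is inferred.** The text does not state how many slopes there are, the word covariates is plural, the random-effect structure is brief, and detail of this kind may sit in an analysis plan that is not shown. This stands in part. One slope is the ordinary reading of a visit's own baseline entered as a covariate, and the stated rationale, "while accounting for the variation in activity between participants by means of the random effect and baseline adjustment", is exactly the use that does not help a paired contrast.

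3. **The adjustment does not only add noise.** A reader might conclude that it should be dropped. When visits truly differ and baseline and outcome share that difference, it helps. At visit SD 0.5, fully shared, the SD of the contrast was 0.124 with one slope, 0.119 with the split and 0.159 with no baseline. Since the protocol itself expects health to change over time, zero visit variance is the extreme case and not the central one.

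4. **Splitting alone does not restore the error rate.** With visit SD 0.3 and a participant effect only, the split model still rejects at about 14%. Most of that excess comes from the missing visit-level error, so the remedy needs both parts.

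The inflation and the power loss also belong to different models: the first to one without a visit-level term, the second to one with it. They are alternatives and should not be added together.

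**Conclusion.** The point holds for the between-visit contrast of 7-day mean activity, on the ordinary reading of the Primary analysis section. The estimate is essentially unbiased, but a single slope makes it less precise than the crossover allows.

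The size rests on variances that the protocol does not give. With a visit-level error and between-person SD 1, the loss is about 32–36 percentage points of power with no visit variance (39% against 71–75%). At visit SD 0.3 it is about 14–21 points (62% against 76% fully shared; 60% against 81% at correlation 0.5). It is negligible at visit SD 0.6, although power there is near its ceiling. With a participant effect only, type I error is about 11–16% against 3–6% when visits do not vary; when they do, most of the excess has another cause.

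This is a pilot sized to estimate an SD, with no stated alpha or power, so no stated figure is overturned. The change is worth making because it is cheap and concerns the estimate closest to the Aim 1 hypothesis.

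**What to change.** In the Primary analysis section:

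- Replace the visit's baseline covariate with two covariates, each with its own slope: the participant's mean baseline over both study visits, and each visit's deviation from that mean.
- Add a visit-within-participant random effect, or an equivalent serial-correlation structure, to the primary model.
- State that the between-visit contrasts come from this model.
- Use the same form for the accelerometer endpoints under Secondary endpoint analysis.

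The cost is one extra slope and one variance component, with no new data. In the settings run, the split with a visit-level error kept type I error near 5% and was never less precise than the single slope. Against no baseline at all it gave up at most about 4 points of power when visits did not vary (0.71 against 0.75), and it gained 8 to 29 points when they did.

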### Intervention

Those randomized to transfusion will receive the standard-of-care-ordered RBC transfusion. This means that they will receive the transfusion as specifically ordered by their primary physician, typically one to two units of allogeneic RBCs. Those randomized to the no-transfusion arm will be discharged from the AIC without receiving an RBC transfusion. The patients who are randomized into the transfusion group will be crossed over into the no-transfusion group and the patients who are randomized into the no-transfusion group will be crossed over into the transfusion group at a subsequent visit. The time of this crossover for a given patient will be at their next scheduled transfusion that is no less than 1 week from the time of their most recent RBC transfusion in this trial.

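### The fixed 7-day outcome window is not ended at the next study visit, so a crossover visit permitted at one week, or sooner after a control visit, can fall inside the first period's window

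*Protocol article*

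**What the plan says.** Four statements in the protocol article bear on this.

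- **Time unit** (General descriptive statistics and preliminary data screening): "For the primary analysis, we will aggregate the summaries on a daily basis".
- **Time scale** (Primary analysis): the outcome is daily total energy expenditure, and time is "days from transfusion or control visit".
- **Window and purpose of the cut** (same section): the model will "consider the 7 days after transfusion/control visit in the model. This censoring of data beyond 7 days after the transfusion/control visit is to avoid carryover" between periods.
- **Crossover timing** (Intervention): at the "next scheduled transfusion that is no less than 1 week from the time of their most recent RBC transfusion in this trial".

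The Discussion calls the interval a 1-week washout. The Secondary endpoint analysis uses the same 7 days for the mean that is correlated with the PROMIS score. The article does not say whether the visit day is counted, or how a day that contains the second study visit is handled.

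**The concern.** The article fixes the time unit, the window length, its reason and the minimum interval. The difficulty comes from how these rules combine at the shortest permitted gap. The cut removes data later than day 7 but takes no account of when the other intervention happens, so it does not necessarily keep the two periods apart, which is its stated purpose.

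A day that contains the second study visit is not a day at home after the first intervention. It includes time at the infusion center and the hours after the opposite intervention. The stated primary test is the transfusion-by-day interaction, and if day enters as a linear term the last day carries one of the two largest weights. The efficacy signal also feeds the decision on a larger trial (Aims and objectives, Secondary), so a misassigned day could matter beyond this pilot.

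**Working it through.** **Plan's own figure.** The article gives no number for this overlap. Its one computed design figure reproduces: 12 × 2 = 24 evaluable, and 24 × 1.25 = 30. Only the 24 is used below.

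**Step 1. Which days overlap.** Inputs: a 7-day window and daily totals (Statistics), and a minimum interval that runs "no less than 1 week from the time of their most recent RBC transfusion in this trial" (Intervention). The gap is the number of days between the two study visits.

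| Gap | Days 1–7 (visit = day 0, not counted) | Days 0–6 (visit day counted) | 168 elapsed hours |
|---|---|---|---|
| 8 days | none | none | none |
| 7 days | second visit on day 7 | none | none |
| 6 days | second visit + 1 later day | second visit | 168 − 144 = 24 h |
| 5 days | second visit + 2 later days | second visit + 1 later day | 168 − 120 = 48 h |
| 4 days | second visit + 3 later days | second visit + 2 later days | 168 − 96 = 72 h |

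At a 7-day gap the share affected is 1/7 = 14.3% of the period-1 days under the first convention, and zero under the other two.

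**Step 2. Which gaps the wording permits.** In the transfusion-first sequence the minimum binds, so 7 days is the shortest gap. In the control-first sequence no in-trial transfusion has yet occurred, so the wording sets no minimum from the control visit. The rows below 7 days are therefore possible in that sequence, and there all three conventions give some overlap.

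**Step 3. Illustrative size at a 7-day gap.** The article gives neither the share returning on day 7 nor the activity lost on a visit day. Assumptions: no true effect, 24 participants in two equal sequences, independent daily values with SD 25% of the mean, and a visit-day loss of 30% for a transfusion visit and 10% for a no-transfusion visit. The test is simplified: a linear day slope per visit, then a one-sample t-test of the slope difference at a two-sided 5% level, which is also assumed.

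In control-first participants the control window loses 30% on day 7. In transfusion-first participants the transfusion window loses 10%. If all return on day 7, the transfusion-minus-control bias is:

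- 7-day mean: (30 − 10)/7/2 = 1.43% of daily activity.
- Slope: the weight of day d is (d − 4)/28, because the squared deviations 9 + 4 + 1 + 0 + 1 + 4 + 9 sum to 28. Day 7 has weight 3/28 and day 1 has −3/28. The bias is (3/28) × (30 − 10)/2 = 1.07% per day, or 6 × 1.07 = 6.4% from day 1 to day 7.

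Simulated type I error under these assumptions:

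| Share returning on day 7 | Losses (transfusion / none) | Slope bias per day | Type I error |
|---|---|---|---|
| All | 30% / 10% | 1.07% | about 10% |
| All | 40% / 10% | (3/28) × 30/2 = 1.61% | about 16% |
| All | 20% / 10% | (3/28) × 10/2 = 0.54% | about 6% |
| Half | 30% / 10% | 1.07/2 = 0.54% | about 6% |
| A quarter | 30% / 10% | 1.07/4 = 0.27% | about 5% |

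With the window ended on the day before the second visit, the slope bias is zero and type I error returns to about 5%.

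**The case against.** The strongest reply is that the article never fixes its day count. Two ordinary conventions give no overlap at a 7-day gap, and the Intervention section's wording suggests elapsed time, under which window and interval simply abut. Day numbering is often left to a full protocol or analysis plan that is not shown here. This stands in part: a reader might infer that the protocol assigns the second visit to day 7, and it does not say so. But days 1 to 7 is the plainest reading of daily totals in the seven days after a visit. Days 0 to 6 would put every participant's own visit day into the window, and no visit-timed 24-hour blocks are described. For the shorter gaps open to control-first participants, the overlap does not depend on the convention.

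The exposed group is unknown and may be small. Crossover waits for the next scheduled transfusion, standing orders act on hemoglobin, and Participants and screening expects a further transfusion within 28 days, not weekly. This stands.

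The direction of bias is assumed. A reader might infer that the overlap favours transfusion, because the infusion takes time. However, if transfusion raises activity, the hours after it would raise the control window instead, and travel to the center could offset time in the chair. No visit-day activity is reported, so the sign is open.

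Finally, the calculation is not the planned model, which adjusts for baseline, uses a random effect and does not commit to a linear day term in the primary analysis. In a linear fit day 1 has the same leverage as day 7. No significance level is stated, and the trial is a pilot sized to estimate a standard deviation. All of this stands and limits what the error rates can show.

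**Conclusion.** The point holds as a flaw in the window definition: the fixed 7-day cut is not closed by the next study visit, so at the shortest permitted gaps it can place the crossover visit day, or days after it, in the period-1 window, contrary to its purpose. At a one-week gap at most 1 of 7 period-1 days is affected, and only if the window is days 1 to 7. At the shorter gaps that the wording leaves open after a first control visit, more is affected.

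The documents do not support a stronger conclusion. The share affected and the direction and size of any bias cannot be determined. The error rates of about 10% to 16% need all 24 participants to return on exactly day 7, under assumed losses and a simplified test. With a quarter returning on day 7 the rate is near nominal. The case for the change is that it is specific, nearly free and valid under any day count, not that serious bias has been shown.

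**What to change.** In Primary analysis, state that the study visit is day 0 and that the outcome window is days 1 to 7 or ends on the last full day before the next study visit, whichever is earlier. Apply the same end to the 7-day mean in Secondary endpoint analysis.

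The cost is one sentence in each place, the loss of one daily value for a participant who returns on day 7, and the loss of more values for control-first participants with shorter gaps. The random effects model can use a shortened window. No change to the visit schedule is needed.

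This does not settle a neighbouring matter. The baseline covariate uses the "mean daily measurements for the 3 days prior to the transfusion/control visit as covariates in the model", and at a one-week gap the second visit's baseline is days 4 to 6, which lie inside the period-1 outcome window under either calendar convention.
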